### Randomization procedures

The randomization sequence will be computer generated prior to the commencement of the study by a trained research assistant, who will be not involved in the study, and maintained in randomized blocks in sequentially numbered sealed opaque envelopes. Eligible participants will be randomly allocated to either the experimental or control group, after the baseline measurements. The training therapist will be responsible for revealing the contents of the sealed opaque envelopes, and therefore, for revealing the allocation.

### Intervention and control

All participants will attend three 40-min sessions per week over 12 weeks [3, 9, 30], in groups of two to four. A trained physiotherapist who has experience with aerobic training will supervise both groups. The exercise intensity will be determined, based upon the results of the cardiopulmonary exercise test [3, 9].

Before and after training, the participants will remain at rest for 10–15 min, during which time their heart rate (heart rate monitor), blood pressure (aneroid sphygmomanometer and stethoscope), and peripheral oxygen saturation (oximeter) will be measured. Heart rate will be continuously monitored. Participants will be asked to report any discomfort and not to undertake any other exercise program during their participation in the present study.

### Experimental group

The participants in the experimental group will perform 5 minutes of warm-up and cool-down treadmill walking, followed by 30 min of aerobic treadmill training at 60–80% of their heart rate reserve [3, 9]. However, for those with poor exercise tolerance, short exercise bouts (for a minimum of 10 min, until they have completed 30 min) may be given initially, with interspersed rest periods [3, 9]. As their exercise tolerance improves, longer periods of continuous exercise with shorter rest periods will be implemented [3, 9]. The progression of the intensity of the treadmill training will be individualized, depending upon the individual’s ability, rate of perceived exertion, heart rate, and blood pressure responses [9]. If they are exercising on the treadmill below their cardiac training range, they will be requested to increase their speed until they are in their cardiac training zone.

### Control group

The participants in the control group will walk outside at a comfortable pace at <40% of their heart rate reserve. If they are exercising above 40% of their heart rate reserve, they will be requested to slow down, until their training zone reaches ≤40%. If the efficacy of the intervention is proved, the experimental intervention will be offered to the participants of the control group at the end of the study.

### Procedures

A trained researcher, who will be blinded to the group allocation, will collect the sociodemographic data and all outcomes.

### Primary outcome measures

The primary outcomes will include both physical activity level and time spent in low-energy expenditure activities, as they are part of the physical activity continuum. Both will be measured by an objective device, the multi-sensor SenseWear Mini®. In addition, physical activity level will be also assessed by a subjective method, the Human Activity Profile (HAP), since objective and subjective methods are complementary, and the questionnaire has the advantage of higher clinical applicability [23, 29].

The multi-sensor SenseWear Mini® (BodyMedia, Pittsburgh, PA, USA; software version 8.1) provides objective measurements of physical activity levels and time spent in low-energy expenditure activities [23]. It is a portable, non-invasive, and lightweight activity monitor [23]. The validity of this multi-sensor has already been established for the measurement of physical activity, compared with indirect calorimetry and double-labeled water [26, 31, 32]. The data acquired by the multiple sensors (heat flux, skin temperature, galvanic skin response, and triaxial accelerometer) are integrated with clinical characteristics (age, height, body mass, sex, and smoking habits) into an algorithm that estimates physical activity levels and time spent in low-energy expenditure activities [23]. This monitor can measure the intensity, frequency, and duration of physical activity and is able to detect improvements in physical activity levels in longitudinal studies with people with stroke [23]. Average daily energy expenditure, expressed in kilocalories, will be used to estimate physical activity levels. The average time spent each day being sedentary, expressed as a percentage of total waking time, will be used to estimate the time spent in low-energy expenditure activities (≤1.5 METs). The participants will use this device, attached to the back of a non-paretic arm [23], for 7 days during each assessment period to reduce the possibility of bias related to differences in physical activity levels and time spent in low-energy expenditure activities for each day during the period [22]. There will be three assessment periods: baseline, post-intervention (after the 12-week intervention), and the 16-week follow-up.

The HAP, which provides subjective measures of physical activity levels [29], will be administered by interviews [29]. It asks about 94 activities, which are hierarchically graded according to their metabolic equivalent [29]. These activities include personal care, transportation, home maintenance, social and leisure activities, and exercise [29]. The HAP Adjusted Activity Score is calculated by subtracting the number of activities that the participant has stopped doing from the number of the last item on the list that they still doing [29]. The Adjusted Activity Score is a better estimate of average energy expenditure spent by an individual [29]. The HAP is commonly used in studies with people with stroke and has been shown to be suitable for assessing physical activity levels in this population [29].

### Secondary outcome measures

Secondary outcomes will be cardiorespiratory fitness (cardiopulmonary exercise test); endurance (six-minute walk test or 6MWT and shuttle-walk test or SWT); depression (Patient Health Questionnaires PHQ-2 and PHQ-9); mobility (comfortable and maximum gait speeds); quality of life (Stroke-Specific Quality of Life Scale or SSQOL); and participation (Stroke Impact Scale or SIS). All measures are suitable for evaluating post-stroke individuals [33–40].

Cardiorespiratory fitness (peak oxygen uptake VO_2peak_ and ventilatory threshold) will be measured using a cardiopulmonary exercise test with a gas analyzer (CPX Ultima Medical Graphics®, USA) and an electrocardiogram. This is an objective, non-invasive, and widely used test, and it is considered to be the gold standard for evaluating cardiorespiratory fitness [35]. The cardiopulmonary exercise test is feasible and safe for people with stroke [3, 41]. The test will use an electronic treadmill, with a progressive ramp protocol [42]. It will follow the recommendations of the American College of Sports Medicine [35]. All tests will be monitored by a cardiologist, who has advanced life support training.

Endurance will be measured using the 6MWT and the SWT [38, 39]. Although the cardiopulmonary exercise test is the gold standard for measuring aerobic capacity, its use in clinical practice is limited, due to the need for specialized equipment and trained personnel [35, 38]. Clinical alternatives are sub-maximal exercise tests, such as the 6MWT and the SWT. These tests are simple and inexpensive, and do not require advanced training [38, 39]. For the 6MWT, the maximum distance covered will be measured [39]. The SWT is an incremental test that consists of 12 levels whose speed is set by an audible signal. It is held in a 10-m track [39].

Depression will be assessed by the PHQ-9 and PHQ-2 [36]. The PHQ-9 is used to assess the frequency of nine depressive symptoms over the previous 2 weeks [36, 43]. The PHQ-2 includes only two of the nine questions [36, 43]. As recommended, the PHQ-9 will be applied, by interview, only for those participants who have a positive outcome on the PHQ-2 [36, 43].

Mobility will be evaluated by both comfortable and maximum gait speeds during a 10-m walk test [38]. The instructions will be standardized and only one trial will be employed [44, 45].

Quality of life will be measured using the SSQOL [34], which consists of 49 items distributed into 12 domains (energy, family roles, language, mobility, mood, personality, self-care, social roles, thinking, upper extremity function, vision, and work/productivity) [34]. The SSQOL is applied by interviews and does not take long to administer [34].

Participation will be measured by the social participation section of the SIS 3.0 [37]. The items on participation are evaluated in terms of frequency of self-reported participation restriction over the previous month [37].

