## Methods/design

A superiority parallel-group randomized controlled trial, with concealed allocation and blinded assessments, will be carried out. A trained researcher, blinded to the group allocation, will collect the written consent and the outcome measures at baseline, post-intervention (after the 12-week intervention), and at the 16-week follow-up, i.e., 4 weeks after the cessation of the intervention (Fig. 1). The examiner will be blinded to group allocation, and the participants and the treating physiotherapist will be asked not to share any information about the intervention with the examiner. Moreover, evaluations will be carried out in different places. Participants will be randomly assigned to either (1) aerobic treadmill training (experimental group) or (2) walking outside (control group) (Fig. 2).

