### Statistical analyses

Each participant will be assigned a unique ID. Two independent examiners, who will be blinded to the group allocation, will enter the data into a computer and verify any missing or apparently wrong values. The original paper forms will be kept in a secure place. The electronic files will be available only to the research team.

An independent examiner, who will be blinded to group allocation, will perform the statistical analysis, using the software SPSS (SPSS Inc., Chicago, IL, USA). Descriptive statistics will be calculated for all outcomes.

The effects of the interventions will be analyzed from the collected data using intention to treat. Data from the last available assessment will be used for missed sessions. Between-group differences will be evaluated using two-way repeated measures ANOVA, considering the baseline, post-training, and follow-up measurements. If there are baseline differences between the groups, analysis of covariance will be used to eliminate the influence of extraneous factors, such as baseline cardiorespiratory fitness, physical activity levels, and time spent in low-energy expenditure activities. The level of significance will be set at 5% and adjusted for multiple comparisons. Data distribution and equality of variance will also be analyzed, to ensure the parametric analysis has been applied correctly.

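### PHQ-9 is a named secondary outcome but is collected only from participants who screen positive on PHQ-2, so it cannot be compared in all randomised participants

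*Protocol article*

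**What the plan says.** Protocol article, Secondary outcome measures: "Depression will be assessed by the PHQ-9 and PHQ-2". The same section adds that "The PHQ-2 includes only two of the nine questions", and then limits the longer instrument: "the PHQ-9 will be applied, by interview, only for those participants who have a positive outcome on the PHQ-2".

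Protocol article, Methods/design: the blinded researcher collects the "outcome measures at baseline, post-intervention (after the 12-week intervention), and at the 16-week follow-up".

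Protocol article, Statistical analyses: "The effects of the interventions will be analyzed from the collected data using intention to treat". Group differences are tested by "two-way repeated measures ANOVA, considering the baseline, post-training, and follow-up measurements". On incomplete data, the section says: "Data from the last available assessment will be used for missed sessions".

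The article does not say whether the PHQ-2 screen is repeated at each assessment, what PHQ-9 value a screen-negative participant receives, or which of the two scores is compared between arms.

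**The concern.** Screening first and measuring severity only in positives is a sensible clinical pathway, but it does not give an outcome that can be compared between randomised arms. Anyone negative on PHQ-2 has no PHQ-9 total. After randomisation a negative screen may itself be the result of treatment, so the scored participants in the two arms need not be alike. The participants who improve most are the likeliest to have no score.

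At stake is the PHQ-9 part of one secondary outcome. An intention-to-treat comparison at three times calls for a score from every randomised participant at each time, and the collection rule prevents this for PHQ-9. A later analysis plan cannot recover seven items that were never asked.

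**Working it through.** **Inputs from the article.** 11 participants per arm (Sample size calculation); three assessment times (Methods/design); PHQ-2 is two of the nine PHQ-9 items (Secondary outcome measures). The article gives no figure for depression, so there is none to reproduce.

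**Assumed inputs, not in the article.** Proportion positive on PHQ-2, p = 20–50%; proportion of baseline positives who turn negative, r = 30–50%; PHQ-2 cut-off of 2 or 3.

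**Step 1: how many participants have a PHQ-9 score.** Expected number per arm at a visit = 11 × p.

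| p | 11 × p | Still positive at the second visit, 11 × p × (1 − r), r = 50% to 30% |
|---|---|---|
| 20% | 2.2 | 1.10 to 1.54 |
| 30% | 3.3 | 1.65 to 2.31 |
| 40% | 4.4 | 2.20 to 3.08 |
| 50% | 5.5 | 2.75 to 3.85 |

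At p = 20% the binomial chance that an arm has at most one PHQ-9 score is 0.8^11 + 11 × 0.2 × 0.8^10 = 0.086 + 0.236 = 0.32. These counts are before any dropout.

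**Step 2: what each way of handling the blanks does, if the screen is repeated.**
- Scores observed at a visit: the groups compared are defined by a post-randomisation result.
- Complete cases in the ANOVA: only participants positive at all three times remain, so anyone who recovers leaves the analysis.
- Last available assessment: a baseline-positive participant who recovers is scored as unchanged.

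**Step 3: illustrative size.** Simulation with 200,000 per arm: nine items scored 0–3, driven by one latent severity, with a baseline-to-post latent correlation of 0.7. The treatment effect is in latent SD units. The last four columns are experimental minus control in post-treatment PHQ-9.

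| Cut-off | Effect | Positive at baseline | Positive after treatment, exp. / control | Everyone | Post-positives only | Baseline-positives, true | Baseline-positives, carried forward |
|---|---|---|---|---|---|---|---|
| 2 | 0 | 32% | 33% / 32% | 0.0 | 0.0 | 0.0 | 0.0 |
| 2 | 0.5 | 33% | 19% / 33% | −2.0 | −1.5 | −2.8 | −1.0 |
| 2 | 1.0 | 33% | 10% / 33% | −3.4 | −2.7 | −5.0 | −1.0 |
| 3 | 0 | 17% | 17% / 17% | 0.0 | 0.1 | 0.0 | 0.0 |
| 3 | 0.5 | 17% | 8% / 17% | −2.0 | −1.4 | −3.0 | −0.6 |
| 3 | 1.0 | 17% | 4% / 17% | −3.4 | −2.5 | −5.5 | −0.5 |

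With a treatment effect, the share of participants who have a PHQ-9 score differs by arm and the observed contrast shrinks. With no effect, every version is about zero. At cut-off 2 and effect 0.5, baseline-positives who turn negative truly change by −5.6 points on average; carry-forward would record 0. The last column applies only if the carry-forward rule is used for these blanks.

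**The case against.** Several points on the other side are sound.

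- **PHQ-2 exists for everyone.** A reader might infer that the trial cannot estimate any depression effect by randomised group. The article does not support that: PHQ-2 is also a named depression measure, it is the screen, and it can be compared in all randomised participants. Only PHQ-9 is affected.
- **The carry-forward rule may not apply.** A reader might infer that the plan will score recovered participants as unchanged. The rule refers to missed sessions. Someone who attends and screens negative has not clearly missed anything, and the sections on withdrawal and intervention use *sessions* for training. The text neither applies the rule to these blanks nor excludes it, so this harm is conditional.
- **Repeat screening is not stated.** Allocation follows the baseline measurements (Randomization procedures). If the screen were applied once, at baseline, the scored subset would be fixed before randomisation and the selection problem would go. PHQ-9 would still be missing in baseline negatives, new cases would be missed, and the numbers would remain small.
- **A statistical analysis plan may settle the handling.** It may say which score is analysed and how blanks are treated. It cannot supply answers that were never collected, so the collection rule remains a fair point.
- **Importance is limited.** Depression is one of six secondary domains, and the Background itself calls secondary outcomes exploratory.
- **The sizes are assumed.** Prevalence, cut-off, correlation and effect are not in the article.

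**Conclusion.** The point holds for PHQ-9 and no further. The article names PHQ-9 as an outcome and then withholds it from screen-negatives, which does not fit an intention-to-treat repeated measures ANOVA over three times. If the screen is repeated at each visit, the participants scored after randomisation are also selected by a result that treatment can change.

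About 2.2 to 5.5 of 11 per arm would have a score at a visit, and 1.1 to 3.9 at both baseline and post-training, under the assumed positive and recovery rates. In the simulation, restricting to post-positives shrinks a true difference of −2.0 to between −1.4 and −1.5, and one of −3.4 to between −2.5 and −2.7. This is attenuation and lost information: under no treatment effect the contrasts are about zero, so nothing here suggests a spurious benefit. The primary outcomes are untouched. It is worth correcting because the correction is cheap.

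**What to change.** Either of two changes resolves it.

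1. Ask all nine PHQ-9 items of every participant at each remaining assessment and analyse the total in all randomised participants. Cost: 9 − 2 = 7 more interview questions per visit for those who screen negative. Recruitment began in August 2017, so PHQ-9 cannot be recovered for screen-negatives already assessed.
2. Name the PHQ-2 score in all participants as the depression outcome compared between arms, and report PHQ-9 only descriptively. This adds no data collection and also covers participants already assessed. The price is a comparison based on two items instead of nine.

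If PHQ-9 remains conditional on the screen, state whether the screen is repeated at each assessment, and state that the last-available-assessment rule does not apply to a PHQ-9 omitted after a negative PHQ-2.

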### Data monitoring committee

The study will not have a data monitoring committee, since aerobic training rarely has adverse effects [9]. However, participants will be monitored during the exercise sessions, to identify any kind of signals or symptoms, such as pain, dizziness, and loss of balance, that would require interruption of the exercise session or their exclusion from the study. In addition, participants will be asked to report any discomfort, which will be registered and reported.

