## Background

Stroke has a high prevalence worldwide [1] and people with stroke are more likely to require help with mobility, self-care, and household activities [2]. Furthermore, they are 40% more likely to have limitations in performing activities compared to matched controls [2]. Furthermore, people with stroke are at high risk of being affected by other cardiovascular diseases or recurrent stroke, which are often associated with the severity of the stroke [1]. Thus, it is important to develop and implement interventions to prevent and manage the associated post-stroke disabilities and the complications and risk factors associated with recurrent stroke, and to promote functionality [3].

Physical activity has the potential to influence several functional domains and health status in individuals with stroke [3]. Physical activity is defined as any bodily movements produced by the skeletal muscles that result in energy expenditure, such as those performed during activities of daily living at home, at work, during leisure, or transport [4]. Exercise is a type of physical activity with specific characteristics: it is repeatedly performed, in a planned and structured way, to improve or maintain physical fitness [4]. Sedentary behavior, which is part of the physical activity continuum and has an independent impact on health, was recently defined as any behavior performed while awake that involves energy expenditure ≤1.5 metabolic equivalents (METs) while in a sitting, reclining, or lying posture [5].

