## Discussion

Although the efficacy of aerobic training in improving VO_2peak_ in individuals with stroke is well known, it is unknown if this training improves physical activity levels and reduces the time spent in low-energy expenditure activities. In fact, it is still unclear which interventions can improve physical activity levels and reduce time spent post-stroke in low-energy expenditure activities. Therefore, the results of this randomized controlled trial will likely provide valuable new information regarding the effects of aerobic treadmill training on physical activity levels and time spent in low-energy expenditure activities for individuals with stroke. Since low levels of physical activity are associated with risk of cardiovascular disease, the investigated intervention may help to improve functionality and health status and reduce the burden of care on the families of people with stroke. Whether exercise improves function and quality of life and prevents secondary diseases, such as stroke, is a high priority research objective, which may be answered by this study [47].

Considering that previous randomized controlled trials have rarely investigated the effects of aerobic training on physical activity levels and that none have investigated these effects on the time spent in low-energy expenditure activities or have used a multi-sensor monitor to measure these outcomes, this study may increase the use of evidence-based practice in that domain, and, hence, may improve the care of people with stroke.

This trial design does have some limitations. It will include a convenience sample, which may limit generalizability. Furthermore, both the participants and the physiotherapist, who will provide the interventions, will not be blinded (Additional file 1).

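### Active harm monitoring is described only for exercise sessions and no harm event is a listed outcome, yet the Discussion says the study may answer whether exercise prevents stroke

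*Protocol article*

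**What the plan says.** The section Data monitoring committee waives a committee on the ground that adverse effects of aerobic training are rare, and then states what is done instead. There are two channels.

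- **Monitoring in sessions:** "participants will be monitored during the exercise sessions, to identify any kind of signals or symptoms, such as pain, dizziness, and loss of balance". The stated purpose is to detect problems "that would require interruption of the exercise session or their exclusion from the study".
- **Self-report:** "participants will be asked to report any discomfort, which will be registered and reported". Intervention and control repeats the request: "Participants will be asked to report any discomfort and not to undertake any other exercise program during their participation in the present study". Neither place gives an event list or a schedule of questions.

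The cardiopulmonary exercise tests have separate cover: "All tests will be monitored by a cardiologist, who has advanced life support training".

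On outcomes, Procedures says: "A trained researcher, who will be blinded to the group allocation, will collect the sociodemographic data and all outcomes". The assessments are at baseline, after the 12-week intervention and at week 16. The outcomes listed under Primary and Secondary outcome measures contain no fall, cardiovascular event, stroke, hospital admission or injury.

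The Background says that "people with stroke are at high risk of being affected by other cardiovascular diseases or recurrent stroke". The Discussion has a sentence on whether exercise improves function and quality of life, which continues that whether it "prevents secondary diseases, such as stroke, is a high priority research objective, which may be answered by this study".

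**The concern.** The harms method is a stated one, offered as the substitute for a committee, and it is weaker than the trial's existing visits allow. Its active part serves decisions about a session or a participant. No count by randomised group is described. The other part depends on the participant thinking that an event counts as discomfort; a hospital admission or a fall at home may not come to mind under that word.

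The people most exposed to this are those who stop attending, some of whom may stop because of an event. Participant withdrawal describes no harm follow-up for them. Methods/design also asks participants not to share information about the intervention with the blinded examiner. That is sound for blinding, but it makes it less likely that a training injury is mentioned at the assessment visits.

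Two things are at stake. A short list of reported discomforts could be read as evidence of safety when it partly reflects how harms were sought. And the Discussion raises an expectation about stroke prevention that neither the outcomes nor the size of the trial can meet.

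**Working it through.** The article states no figure on this point, so there is none to reproduce. The check has two parts.

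**1. Which periods have a described route for a serious event?**

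| Period | Active monitoring described | Open self-report | Harm event among listed outcomes |
|---|---|---|---|
| During a session, weeks 1–12 | Yes | Yes | – |
| Between sessions, weeks 1–12 | No | Not excluded by the text | – |
| After a participant stops attending | No | Unclear | – |
| Weeks 12–16 (4 of 16 weeks = 25%) | No; there are no sessions | Not excluded by the text | – |
| Assessments at weeks 12 and 16 | Cardiologist at the exercise tests | Not excluded by the text | No |

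The sample size section expects 20% dropout: 0.20 × 22 = 4.4, so about 4 participants may fall in the third row.

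**2. Can the trial answer whether exercise prevents stroke?**

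Inputs from the article: 22 participants, 11 per group, 16 weeks, no stroke outcome. The article gives no recurrent-stroke rate, so the rates below are assumptions.

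- Person-years with complete follow-up: 22 × 16/52 = 6.77.
- Expected strokes in both groups together, at an assumed 3–10% a year: 6.77 × 0.03 = 0.20 to 6.77 × 0.10 = 0.68.
- Wider range of assumed annual rates r, with 16-week risk p = 1 − (1 − r)^(16/52). Power is for a halving of p with 11 per group, by the normal approximation for two proportions (two-sided 5%). The approximation is rough at such counts but sufficient for the order of magnitude.

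| r per year | p at 16 weeks | Expected strokes, 22 × p | Chance of none, (1 − p)^22 | Power for a halving | Needed per group for 80% power |
|---|---|---|---|---|---|
| 2% | 0.62% | 0.14 | 87% | 3% | 7,563 |
| 5% | 1.57% | 0.34 | 71% | 4% | 2,971 |
| 10% | 3.19% | 0.70 | 49% | 4% | 1,440 |
| 15% | 4.88% | 1.07 | 33% | 5% | 929 |

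So even perfect recording of every stroke would leave the question unanswered.

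**What a clean harms record could show.** With no event in n participants, the one-sided 95% upper limit is 1 − 0.05^(1/n). For one group of 11 this is 1 − 0.05^(1/11) = 23.8%; for all 22 it is 1 − 0.05^(1/22) = 12.7%. A group with no affected participant is still compatible with a true risk of nearly one in four.

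**The case against.** The strongest reply is that this is silence in a condensed article. Event definitions, collection windows and follow-up after withdrawal are often left to the full protocol, and the schedule in Fig. 1 is not available here. That stands in part: a fuller document may contain an active route, and the point claims only that none is described. It does not remove the point, because the article goes beyond silence. It states a harms method as the replacement for a committee, and it gives an outcome list without harms.

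Several stronger readings are tempting, and the documents do not support them.

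- *Harms are sought only during sessions, and all other events go uncounted.* Self-report is an additional channel with no time limit in the text, and its repetition under Intervention and control can be read as covering the whole period of participation. The text does not say that other events will be ignored.
- *Harms are recorded by unblinded staff.* The article does not say who registers discomfort.
- *The article names falls as a high risk.* The Background names cardiovascular disease and recurrent stroke. Loss of balance appears only as an example of a symptom to watch for in sessions.
- *Sessions cover 36 × 40 min = 24 h of 16 × 168 = 2,688 h, so 0.9% of harms would be captured.* The share of hours supervised is not a capture rate, since a participant can report at any of 36 contacts what happened in the preceding days.
- *The trial will wrongly declare the training safe.* The article sets no safety aim and promises no such conclusion.

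It is also fair to say that the Discussion sentence is hedged and that its first half concerns function and quality of life, for which the trial has measures. The hedge does not rescue the part on secondary diseases, which has no matching outcome.

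**Conclusion.** The concern holds in two limited parts.

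First, the described harms method is active only in sessions and otherwise rests on open self-report, with no harm event among the listed outcomes. A better method is available at a visit that already takes place. How many events would be missed cannot be estimated from the article, and this part is conditional on the full protocol adding nothing.

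Second, the statement that prevention of secondary diseases such as stroke may be answered by this study is wrong as written. It needs a stroke outcome, which is absent, and far more than 6.8 person-years. The expected 0.2–0.7 strokes depends on an assumed 3–10% annual rate and on complete follow-up of 22 participants, but the conclusion is the same from 2% to 15%.

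Neither part affects the comparison on the primary outcomes.

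**What to change.** 1. **Procedures and Data monitoring committee.** At the existing week-16 visit, after all outcome measures are complete, ask every randomised participant, including those who stopped training, one short fixed list of events since randomisation: falls, stroke or TIA, cardiac event, hospital admission, injury. If the list is also used at week 12, someone already on the team other than the blinded examiner should ask it, because answers about events or injuries could reveal allocation before the week-16 assessment.
2. **Reporting.** Give the number of participants with at least one event by randomised group, with the number asked in each group. Keep this separate from the session log and treat it as description only, with its confidence limit (about 24% for 0 of 11).
3. **Discussion.** Delete the statement that prevention of secondary diseases such as stroke may be answered by this study. Function and quality of life may stay, since the trial measures them.

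Cost: a few minutes per participant, one form, one table and one edited sentence. The downside is some recall error over 16 weeks. If the full protocol already contains such a question, the first change reduces to stating it in the article.
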